#### Outcomes and data analysis

The primary outcome measure will be the percentage of smokers reporting 6-month sustained abstinence at the final follow-up, with supplementary analyses of the percent making a quit attempt assessed at 2-week post-implementation date, and point-prevalence abstinence at each follow-up point. The primary analyses will use intention to treat analysis with various strategies for dealing with missing data (all will be followed up regardless of engagement with the interventions). Some analyses will be conducted using only reported outcomes, especially those that involve possible mediators or moderators of effect, which will include logistic regressions. Biochemical validation of cessation outcome is considered unnecessary in larger population-based studies (particularly where there are low demands on the participants and no face-to-face therapist contact) as levels of misrepresentation are generally low and unsystematic [38]. This is an effectiveness trial where randomisation is to a set of recommendations which we know a significant proportion of participants will not follow. We will monitor both the choices smokers make around timing of implementation and the extent to which they comply with exercises and advice around structured planning as these should mediate outcomes see [39]. In doing so we will ask about any pre-decisional planning and prior quit experience. Nonetheless, the primary analysis will explore condition by outcome, independent of intervention compliance. Important secondary outcomes are whether the proportion of smokers who accept the offer to schedule their quit attempt and/or implement criterion levels of planning differs by condition, and the prospective relationship between those actions and success. We will also assess the impacts of the interventions and the outcomes on measures of quality of life, affect (particularly signs of depression), and overall health. This will be done both as a function of allocated condition and by achieved outcome.

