**Methods/design:**

A complex randomised controlled trial with a factorial design, testing the presence of a recommendation to quit immediately (or not) and encouragement to structured planning (or not) as additions to standard care, a web-based automated tailored advice program (QuitCoach). Participants are recruited from users of the QuitCoach who reside in Australia, do not report a mental health condition for which they are taking medication, are adult daily smokers, and at least open to the possibility of quitting. For the Immediate arm they could not have committed to quit within 2 days, while the Planning arm included all these and those quit within the last 4 days. This creates 6 groups: 2 × 3, with 2 × 2 fully randomised, and 2 only randomised for the planning arm. Follow-up assessments are conducted around 1 month (targeting two weeks after the quit attempt started), and 6 months later. The primary outcome is 6-month sustained abstinence at 6 months. Secondary outcomes include point-prevalence abstinence at both follow-ups, and making quit attempts during the intervention period. We will also explore differences in actual behaviour (timing and planning) by intervention, and relate this to outcomes.

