**The immediate implementation arm (IC and IP groups)** This involves a modified version of the standard QuitCoach with key elements of the intervention delivered during the assessment stage. Those in this arm are encouraged (recommended) to quit immediately, or as soon as practically possible, during their initial QuitCoach assessment (and any subsequent assessments, if they have not already quit) (‘We suggest you think about setting a quit date right now. There is nothing to be gained by delaying it’). They are provided with a brief explanation of the reasons for doing so: that some recent research suggests that quitting as soon as you decide may increase the likelihood of success over delaying implementation. Those who have already set a quit date are encouraged to bring their quit date forward (‘We suggest you bring your quit date forward, as there is nothing to be gained by delaying it. Choose the earliest time you can’), ideally quitting immediately, later today or first thing tomorrow morning. Others are encouraged to take the next step toward quitting as soon as possible (e.g. for those planning to take prescription medication ‘We recommend you call the doctor to make an appointment immediately’), implement their quit attempt immediately they have done all they need to do, and to do this preliminary work in as short a period as possible (e.g. for those planning to cut down, ‘if you want to cut down, take no more than 4 more days to quit completely’). This is all done during the assessment phase. In addition, any commitment to immediate implementation is reinforced in the advice letter, and for those not taking up the suggestion during the assessment, they are encouraged to implement as soon as they feel ready to commit.

**The structured planning intervention** The structured planning augmentation of the QuitCoach (the IP, CP and XP arms of the study) consists of additional highly prescriptive instructions for planning a quit attempt, organised around two main tools; a To Do List (TDL) and a Problem Planner (PP). The To Do List operates something like the Task function in some computer diaries. It prompts the user by listing the most important things they need to do to increase their chances of quitting smoking successfully, with an indication of when they need to be done. The Problem Planner provides a template for the development of implementation intentions to survive identified problem situations.

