**Integration of the two interventions (IP group)** Because the Structured Planning intervention is tailored to any level of immediacy in quitting, there is nothing unique about this group except that more will be doing their planning after the initiation of their quit attempt and more after full implementation (as will the XP group).

**Common elements** Frequency of use of the QuitCoach is at the participant’s discretion, regardless of which of the four possible study arms they have been randomised to. Thus, there is no set endpoint for delivery of the intervention. All participants will be reminded to return to the site via emails sent periodically over several weeks, scheduled according to their readiness to quit.

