#### Assessment tools

We collect research information at three points: 1) at baseline, incorporated into the QuitCoach assessment (nearly all questions used are part of the standard assessment); 2) a first follow-up two weeks after the estimated quit date for each participant, or where the quit date is unknown or a quit date has not been set, a month after recruitment; and 3) A final follow-up 6 months after the identified quit date for each participant, or a comparable time after recruitment if no quit attempt was reported at the initial follow-up. Follow-up assessments will be conducted over the Internet, using email invitations including a web link to prime respondents to do the surveys online, or for those failing to respond to this, by telephone interview (the emailed invitation includes a notification that those failing to respond will be called).

The QuitCoach assessment, used as the baseline survey, includes validated measures of sociodemographics, quitting history, intention to quit [29], self-efficacy to quit [29], nicotine dependence [30], pros and cons of smoking and temptations to smoke [31], determination to quit [32] and a 5-item measure of positive and negative affect. All of these are used in the advice tailoring algorithms. To this we have added measures of rated quality of life, health status, perceived usefulness of planning, and the extent to which planning has already taken place on the current quit attempt (prior to recruitment). The base assessment will also ask for residential details (i.e., postcode) with which to determine socio-economic status as measured by SEIFA levels of area disadvantage [33].

At the first follow-up, we will assess smoking status, including implementation of the suggested quit date and actual quit date. We will ask about the extent of any planning undertaken since the baseline survey both pre- and post-full implementation of quit attempts (as relevant). We will measure use of other cessation support and use of pharmacotherapy (both pre-and post-implementation). The questions on affect will be re-asked in order to assess stability of mood. Finally, among those quit, we will measure self-efficacy to stay quit, extent of cravings [34], and determination to stay quit [32].

The final (6-month) follow-up will be restricted to measuring outcomes; smoking status, duration of time quit, and any lapses.

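### Quit attempts are counted at a first follow-up whose date the Immediate advice itself moves, so the arms are compared over unequal windows, with bias of unknown size and sign

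*Protocol article*

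**What the plan says.** The protocol article words this outcome in two ways. The abstract has "Secondary outcomes include point-prevalence abstinence at both follow-ups, and making quit attempts during the intervention period". The Outcomes and data analysis section has "supplementary analyses of the percent making a quit attempt assessed at 2-week post-implementation date". On the length of the intervention, the Common elements paragraph under Interventions states: "Thus, there is no set endpoint for delivery of the intervention".

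The survey that supplies the outcome is described under Assessment tools. For people who hold a date it is "a first follow-up two weeks after the estimated quit date for each participant". A fallback covers everyone else: "where the quit date is unknown or a quit date has not been set, a month after recruitment". The abstract gives a looser account: "Follow-up assessments are conducted around 1 month (targeting two weeks after the quit attempt started), and 6 months later".

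In the Immediate arm, participants who already have a date are urged during the baseline assessment to bring it forward, "ideally quitting immediately, later today or first thing tomorrow morning". Those without one are urged to set one at once or to take the next practical step. The sample size section expects about 60% to accept.

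The first follow-up asks for the actual quit date. The final survey is limited to smoking status, time quit and lapses.

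**The concern.** Whether someone has made an attempt is a cumulative outcome: the longer the person is watched, the more likely the answer is yes. Here the length of watching is set by the estimated quit date, and the randomised Immediate recommendation is designed to change that date. Allocation therefore affects both the behaviour and the time allowed for observing it.

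Take an acceptor who sets tomorrow as the date, does not act on it, and first quits on day 20. That person is a non-attempter at a day-15 survey. An undated control who first quits on day 20 is an attempter at a day-30 survey. Analysing everyone as randomised does not remove the difference.

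At stake is the reading of the attempt contrast. It is a natural link between the advice to start now and any effect on abstinence, and the Outcomes section plans to study timing choices as mediators.

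**Working it through.** **Inputs from the protocol article**
- First follow-up: quit date D + 14 days, or about 30 days from recruitment if there is no date (Assessment tools).
- Immediate acceptors who stop today or tomorrow: D = 0 or 1, so day 14 to 15. Those cutting down over up to 4 days: 4 + 14 = day 18. Those who first need a prescription: a later date, or no date and the month rule (Interventions).
- Controls with their own date: D is at least 2, so 2 + 14 = day 16 or later (Methods/design, eligibility text below Table 1).
- Acceptance: 60% (Sample size calculation).
- Attempt rates and the share holding dates: not given.

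There is no planned figure for this outcome to reproduce. The primary power of 86% (18% v 23%, 1200 per side) reproduces as 85.9% at two-sided 5%. It uses none of the quantities below.

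**Assumptions.** The estimated date is the one held after the advice. The 40% who do not accept behave, and are surveyed, like controls, so they cancel. The reference is a common 30-day window.

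**Step 1: everyone undated at entry, all acceptors surveyed early.** Let A14 be the share of acceptors attempting by day 14, and h the share of the remaining acceptors who first attempt on days 15 to 30.

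Understatement = 0.60 × (1 − A14) × h

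| A14 | h | Understatement (points) |
|---|---|---|
| 0.5 | 0.3 | 9.0 |
| 0.7 | 0.2 | 3.6 |
| 0.9 | 0.1 | 0.6 |
| any | 0 | 0 |

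If only half of acceptors are surveyed early and the rest at a month (assumed), 0.60 becomes 0.30 and the top value falls to 0.30 × 0.5 × 0.3 = 4.5 points.

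**Step 2: outer case, accepting a date changes nothing.** All undated, constant hazard, 30-day attempt rate m, acceptor window w days:

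r = 1 − (1 − m)^(w/30); spurious difference = 0.60 × (r − m)

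With m = 0.5 and w = 15, r = 0.293 and the difference is 0.60 × (0.293 − 0.5) = −12.4 points. For m from 0.3 to 0.7 and w from 15 to 18, it runs from −6.4 to −14.9 points.

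**Step 3: some controls hold dates.** Assume acceptors reach 90% by day 14 and 92% by day 30. Assume controls with D = 3 (window 17 days) reach 75% by day 17 and 82% by day 30, and undated controls 50% by day 30. Among dated people the observed gap between acceptors and comparable controls is 90 − 75 = 15 points, against 92 − 82 = 10 at a common month, so the effect is overstated. With dated share q:

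Net bias = 0.60 × (−0.02 + 0.07q)

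For q = 0, 0.25, 0.50 and 0.75 this is −1.2, about −0.2, +0.9 and about +2.0 points. It crosses zero near q = 0.02/0.07 = 0.29.

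Other dated rates reverse the sign again. Acceptors at 70% then 80%, with controls at 60% then 66%, give 10 observed against 14 at a common month.

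**Can the planned data repair it?** Only in part. The actual quit date allows attempts to be placed in time up to each person's survey. Time quit at the final survey would show a later attempt that is still holding. No listed item captures an attempt begun after an early survey that then failed.

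**The case against.** The case against has five parts.

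- **The two wordings are mostly one.** The abstract is shorthand, the two-week reading is simply the first follow-up, and the month rule covers people who never start. The open-ended statement concerns delivery of the program, not measurement. This largely stands: the wording needs harmonising, but there are not two rival endpoints.
- **The early survey is a floor.** The Background says immediate implementation means taking the next step, and that only some will stop at once. The abstract puts this survey at around a month, and email non-responders are chased by telephone. This stands and shrinks the gap.
- **Controls may hold dates,** so their windows are shortened too. This stands, and it is why the sign is open.
- **The outcome is minor.** The Outcomes section treats attempts as supplementary, and the secondary outcomes it calls important are take-up of scheduling and criterion planning. This stands as a limit on weight.
- **Actual quit dates already allow a fair 14-day comparison,** which an article may leave to the analysis plan. The data point is right and makes the repair cheap. But the article does more than leave the window open: it fixes the reading at a survey whose timing depends on the quit date.

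A reader might infer that the Immediate effect on attempts is understated, or attach a false-positive rate to the contrast. The documents support neither. Both require all acceptors to be surveyed at about day 15 and all controls at day 30, and the eligibility and intervention texts do not say that.

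**Conclusion.** The concern holds as an unequal-window problem on a secondary outcome. As written, the Immediate versus own-timetable contrast on attempts compares about two weeks of observation for prompt acceptors with 16 days or more for dated controls and about a month for undated participants.

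The bias has no size or sign that the documents fix. It most plausibly runs against Immediate if most participants are undated. It may be near zero or positive if many controls hold dates or nearly all acceptors act at once. The calculated ranges show only what assumed attempt rates would imply; they are not estimates for this trial.

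The primary outcome's power calculation is unaffected by this point. The change is worth making because a contrast whose bias could go either way cannot be interpreted, and the repair is small.

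**What to change.** In the abstract and in Outcomes and data analysis, replace both wordings with one definition: first quit attempt begun within a fixed number of days of randomisation, the same in all four cells of the 2×2. Score it from the actual quit date collected at first follow-up, taken as the date of the first attempt since recruitment.

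- **About 14 days.** This is no longer than the shortest planned follow-up, so it needs no new data. It partly measures timing and favours Immediate by design, and should be labelled that way.
- **30 days.** Add one item on the date of the first attempt since recruitment, put in the same way and at the same time to every group, for example to all participants at the final survey. Do not ask it only of early-surveyed people who had reported no attempt. They would be disproportionately Immediate acceptors, and the recall error would then differ by arm. The final survey is itself timed from the quit date where there is one, so word the item from the recruitment date and keep the recall interval as equal as practicable.

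The cost is one definition and, for 30 days, one survey question, with no added participants or visits. The downside is recall error: the Background puts forgotten attempts at 20% or more within a year.

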#### Ethical review

The study protocol was approved by the Cancer Council Victoria Human Research Ethics Committee (HREC No. 1108).

## Discussion

This study will result in a better understanding of the roles of planning and delay in influencing quit attempts. It is the first large-scale population test of the utility of implementation intentions and if it shows they convey real benefits, should lead to their widespread adoption in cognitive behavioural interventions generally. It will also lead to advances in our understanding of how hard-to-change behaviours can be modified. This will allow us to provide advice both to smokers thinking of quitting, and to smoking cessation services, of the optimal way to configure quit attempts. We are also likely to have enhanced the capacity of QuitCoach in terms of increased efficacy and participation, thus increasing the potential impact of one component of Australia’s current suite of services for smoking cessation.

If smokers should be encouraged to quit spontaneously rather than delaying in order to plan, it has profound implications for the delivery of all cessation services. It would demand that help programs have the capacity to respond rapidly, rather than place people in queues to be managed on the service’s timeline.
